## Abstract

The aim of this present clinical trial is to evaluate the effectiveness of a multicomponent prehabilitation programme administered through educational videos versus another programme based on written exercise recommendations, in patients scheduled for lumbar radiculopathy surgery. This study will be a multicentre, controlled, randomised, parallel clinical trial. One hundred participants undergoing lumbar radiculopathy surgery who meet the established inclusion criteria will be recruited at different Spanish hospitals. The experimental group will follow a 4-week prehabilitation programme combining therapeutic exercise, back care education, and pain neuroscience education delivered through videos designed for consumption at home. The control group will be provided with written instructions to perform therapeutic exercises during the same prehabilitation time period. The primary outcome of the study will be disability, assessed using the Spanish version of the Oswestry Disability Index. The secondary outcomes will be pain perception, health-related quality of life, fear avoidance, kinesiophobia, catastrophising, anxiety, depression, physical activity, and the treatment satisfaction of the patients. This study will provide evidence for the effectiveness of a home-based multicomponent prehabilitation programme that addresses some already identified barriers to patient attendance in face-to-face programmes. Understanding the medium and long-term effects of pre-surgery lumbar muscle training and pain neuroscience education administered via instructional videos watched by patients at home, will help improve the design of prehabilitation programmes in this population while also improving the cost-effectiveness of such interventions.

## Introduction

One of the most prevalent chronic pain conditions worldwide is low back pain (LBP), which affects more than 70% of the general population over their lifetimes and with an annual incidence of 40%. In addition, LBP tends to recur or become chronic, which can severely limit the daily quality of life of patients [1]. Lumbar radiculopathy is often cited as an indication for lumbar surgery, especially in the context of failed conservative care and worsening symptoms [2–4]. This condition is defined as unilateral leg pain worse than back pain, with pain radiating to the foot or toes and numbness and paresthesia in the same areas that is associated with a motor neurological deficit [5]. Surgical intervention for radiculopathy resulting from disc herniation and spinal stenosis has been found to yield substantial improvements at 3-month follow-up, yet only modest to moderate enhancements in terms of pain and disability are observed at 5-year follow-up assessments [6, 7]. Indeed, around 20% of patients undergoing surgery for lumbar radiculopathy develop chronic pain after surgery, which suggests that some patients may experience long-term pain and disability after lumbar surgery for radiculopathy, thereby leading to a high socioeconomic burden [8].

These patients usually require postoperative rehabilitation, even though the preoperative period is considered an ideal period for them to prepare for the surgery. Therefore, the concept of prehabilitation is characterized as the process of preparing patients to endure surgical stress more effectively, thereby facilitating expedited recovery through the enhancement of their functional capabilities and physiological reserves prior to undergoing surgery [9, 10]. In addition, prehabilitation has been demonstrated to decrease the likelihood of postoperative complications [11], thus aiding in the mitigation of postoperative pain intensity and duration of hospitalization, while also expediting patients’ return to preoperative levels of physical function[12].

In recent years, neuroscience education has emerged as a prominent educational strategy for patients with chronic LBP. Pain neuroscience education (PNE) is an education intervention based on cognitive learning that aims to reduce pain and disability by helping patients gain an increased understanding of their pain, de-emphasise the anatomopathological content, and focus on the factors that contribute to the development of pain, all within a biopsychosocial framework [13, 14]. PNE consists of educational sessions in which the physiology of the nervous system as well as the neurobiology of pain are explained to the patient in an easy to understand manner through the use of drawings, prepared pictures, examples, metaphors, and leaflets to supplement direct explanations [15]. Thus, PNE is based on improving patient knowledge about pain because, theoretically, it may reduce their pain. This is because pain is often related to fear and disability and so PNE can potentially help improve physical and mental health [16, 17].

Different studies have suggested that pre-surgery physiotherapy and pain education can improve outcomes, both in terms of function and health behaviour in patients with lumbar radiculopathy [11, 14]. Indeed, to date, 5 previous randomised clinical trials (RCTs) [11, 14, 18–20] have investigated the effect of different prehabilitation programmes in patients with lumbar disc herniation, degenerative lumbar spine disorders, or lumbar radiculopathy scheduled for lumbar surgery. First, Nielsen et al. [11] investigated the effects of a 2-month prehabilitation programme which included an intensive exercise programme and optimisation of the analgesic treatment. In turn, Louw et al. [14] investigated whether 1 session of PNE before surgery would improve the surgical outcome. Rolving et al. [18] examined whether a multidisciplinary cognitive-behavioural therapy intervention (6 sessions lasting 3 hours) would be beneficial. Next, in the study by Lindbäck et al. [19], patients received individual sessions of pre-surgery physical therapy twice a week for 9 weeks. Finally, Chu et al. [20] investigated the effects of virtual reality health education measures administered to the patients on the afternoon of the day they were admitted for scheduled surgery.

A recent meta-analysis including 5 RCTs found evidence with a high level of certainty supporting the usefulness of prehabilitation over standard care in terms of reducing preoperative back pain, as well as moderate-certainty evidence that prehabilitation improved health-related quality of life in patients that underwent lumbar surgery. Postoperatively, there was also moderate-certainty evidence supporting the notion that prehabilitation improved function following lumbar surgery after 6 months [21]. While on the one hand, there are currently no guidelines for rehabilitation planning before lumbar spine surgery, on the other, face-to-face prehabilitation may not be feasible for every patient. Therefore, some studies have highlighted the need for alternative preoperative lumbar spine education systems and so recommend exploring prehabilitation programmes based online [22].

To the best of our knowledge, to date, no studies have explored the possibility of a prehabilitation programme integrating patient physical conditioning through therapeutic exercise with PNE administered via videos watched by patients at home. We hypothesise that a multifactorial prehabilitation programme of this type, specifically designed for patients undergoing lumbar radiculopathy surgery, would yield well-informed and trained patients. We anticipate that this intervention would surpass the written instructions approach in terms of mitigating disability, improving quality of life, its the impact on psychological variables, and in the alleviation of back and leg pain. Therefore, the aim of this planned study will be to evaluate, in patients scheduled for lumbar radiculopathy surgery, the effects of a 4-week prehabilitation programme that combines therapeutic exercise, back care education, and PNE delivered through videos consumed by patients at home, compared to a regimen involving therapeutic exercise provided with written instructions. The outcomes we will study are disability, pain, quality of life, psychological variables, physical activity, and the satisfaction of patients with the treatment.

## Materials and methods

### Study design

This study will be a multicentre, controlled, randomised, parallel clinical trial. This study protocol was written in accordance with the Standard Protocol Items: Recommendations for Interventional Trials (SPIRIT) guidelines [23], with the aim of improving the quality of the eventual clinical trial.

### Ethical approval and registration

The design of this study conforms to the principles outlined in the Declaration of Helsinki and the protocol was approved by the Research Ethics Committee at University CEU Cardenal Herrera (reference number CEEI23/459). Participation in the study will be voluntary and will require the written informed consent of each participant. Eligible patients will be informed about all the relevant aspects of this study before starting their rehabilitation programme. The protocol was registered with the United States National Library of Medicine (ClinicalTrials.gov) with identifier NCT06145620 in November 2023. Personal information will be collected by the clinical research coordinators and stored in a database on a password-protected computer in order to protect patient confidentiality.

### Participants: Recruitment and eligibility criteria

One hundred patients will participate in this study and their recruitment is expected to start in January 2024 and continue up to January 2025. The inclusion criteria will be the following: adults aged 18 to 80 years diagnosed with lumbar radiculopathy to whom surgery has been proposed. The predominant symptoms that will justify treatment by surgical decompression will be leg pain, with or without neurological deficits. Participants will be excluded if: (1) they are undergoing any other non-pharmacological treatments or physical therapy designed to address lumbar radiculopathy; (2) surgery with instrumentation (e.g., spinal fusion, arthrodesis, etc.) has been proposed to them; (3) they require acute surgery; (4) they have a concurrent chronic pain condition (e.g., fibromyalgia, chronic fatigue syndrome, etc.); (5) they exhibit symptoms of spinal cord compression; (6) they have been diagnosed with a malignant tumour; (7) they have a mental illness; (8) they have undergone a previous spinal surgery; or (9) they do not have access to an internet-enabled mobile device.

### Randomisation and blinding

The sample will be recruited by the physicians in the Orthopaedic Surgery Services at different Spanish hospitals, who will also be responsible for obtaining the signed informed consent from the enrolled patients. A statistician from outside this research team will generate the random sequence using random number allocation software [24]. Participants will be randomly assigned to the experimental group (EG) or the control group (CG). To achieve a balanced distribution within each group according to sex and age, these variables will be blocked obscured during the patient assignment process. Additionally, randomisation will occur in blocks of 2 participants to ensure equality in the number of patients assigned to each group and also facilitating the possibility of partial and/or interim analyses.

The randomisation sequence will remain concealed throughout the application of the intervention programme and entire data collection procedure. Only the investigator responsible for patient group assignment will have knowledge of this sequence. Thus, the remaining researchers responsible for collecting all the pre-intervention (baseline), post-intervention (immediately after the 4-week prehabilitation), and follow-up assessment (1 month, 6 months, and 12 months after surgery) data will be blinded to the participant group assignments. It will be impossible to blind the participants to their group assignments because of their active role in performing the interventions and the evident differences between their intervention types.

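### A fixed, published block size of 2, with participants who know their group, makes up to half of the allocations predictable to a recruiter who learns the earlier one, so concealment is poorly protected

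*Protocol article*

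**What the plan says.** All of the relevant text is in the protocol article, section Randomisation and blinding.

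- **Block size.** "randomisation will occur in blocks of 2 participants to ensure equality in the number of patients assigned to each group". One size is given, and it is now public. The same sentence adds that this would make partial or interim analyses possible.
- **Balancing factors.** "To achieve a balanced distribution within each group according to sex and age, these variables will be blocked obscured during the patient assignment process". The wording is unclear. Age cut-points, the number of strata and any separation by hospital are not given.
- **Generation.** "A statistician from outside this research team will generate the random sequence using random number allocation software".
- **Recruitment and consent.** "The sample will be recruited by the physicians in the Orthopaedic Surgery Services at different Spanish hospitals"; the same physicians obtain consent.
- **Custody.** "Only the investigator responsible for patient group assignment will have knowledge of this sequence". The text then turns to the other researchers, so the holder reads as a member of the team.
- **Concealment.** "The randomisation sequence will remain concealed throughout the application of the intervention programme and entire data collection procedure".
- **Blinding.** "It will be impossible to blind the participants to their group assignments". The researchers who collect the data "will be blinded to the participant group assignments".

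The Statistical methods section gives the total as 100 patients, 50 per group.

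**The concern.** Concealment matters at enrolment: the person deciding whether and when to enter a patient should not be able to foresee the group. A fixed block of 2 is the smallest possible, and it gives the second allocation away to anyone who knows the first. The route is plausible here. Patients know whether they received videos or mailed instructions, they are awaiting surgery in the services that recruit, and they can tell their physician. Several exclusions, such as mental illness or a concurrent chronic pain condition, leave room for judgement, so a foreseen allocation could affect who is entered and when.

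The concealment sentence does not close this gap, because it describes the period after allocation. The list also passes from an outside statistician to a team member, and the article does not say whether that person is separate from recruitment.

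What is at stake is selection bias. The planned adjustment for baseline values, age and sex would reduce bias from measured differences between the groups, but not from unmeasured prognosis.

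**Working it through.** **Inputs.** Block size 2, total 100 and a 1:1 ratio come from the protocol article. The number of strata K is not given and is an assumption, varied from 1 to 40 with strata of equal expected size.

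**The plan's own figure.** On a single list, 100 / 2 = 50 complete blocks with one patient per group in each, giving 50 and 50. The stated split is reproduced.

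**Predictability with blocks of 2.** The first allocation in a block is a fair toss (best guess right with probability 0.5). The second is certain (1.0).

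- Share determined: 1 / 2 = 50%, or 50 of 100 patients.
- Average correct guesses: (0.5 + 1.0) / 2 = 75%.

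**Other fixed block sizes.** Enumerating all permuted blocks of size b, the share determined by earlier allocations equals 1 / (b/2 + 1). For b = 4, the chance of a correct guess by position is 1/2, 2/3, 2/3 and 1, so the average is 2.833 / 4 = 70.8%. For b = 6 it is 0.5, 0.6, 0.6, 0.7, 0.7 and 1, so the average is 4.1 / 6 = 68.3%.

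| Fixed block size | Determined | Best guess right | Largest imbalance per stratum (b/2) |
|---|---|---|---|
| 2 | 50% | 75% | 1 |
| 4 | 33.3% | 70.8% | 2 |
| 6 | 25% | 68.3% | 3 |

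Without blocking, the figures would be 0% and 50%.

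**With strata.** A stratum with an odd count ends on an open block. About half of K strata have odd counts, so the determined share is close to (100 − K/2) / 200. In 4,000 simulated trials for each K:

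| Assumed strata K | Formula | Simulated share determined | Mean absolute difference between groups |
|---|---|---|---|
| 1 | see above | 50% | 0 |
| 4 | 98/200 = 49% | 49% | 0.9 |
| 8 | 96/200 = 48% | 48% | 1.5 |
| 20 | 90/200 = 45% | 45% | 2.4 |
| 40 | 80/200 = 40% | 40% | 3.5 |

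The correct-guess rate is 0.5 + 0.5 × share, which is 74.5% for K = 4 and 70% for K = 40. Stratifying therefore barely reduces predictability. It also means that blocks of 2 do not strictly secure equal groups.

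**Need for blocks of 2.** Blocks of 4 or 6 also keep the groups nearly equal. No interim analysis is described elsewhere in the article, so nothing in it depends on this block size.

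**The case against.** The strongest reply is that the article separates the roles. Physicians recruit and take consent, an outside statistician generates the list, one investigator assigns, and other researchers collect data blinded. Someone has to hold the list, and the text says the sequence stays concealed. A reader might infer from the custody sentence that allocation is not concealed at all, or that the assigning investigator can time or withhold enrolment. Neither is supported: enrolment and consent are given to the hospital physicians, and the assigning investigator is given no say over who is approached. Nor does the text exclude such a role, and that gap is what remains.

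It can also be said that 50 of 100 is a ceiling. A recruiter has to learn the first allocation in the same block and know that the block is still open. The article does not say that recruiters are told allocations, and the interventions reach patients at home. With one list across hospitals, the block partner will often be at another site. Timing matters as well. At 100 patients in about 12 months, the mean gap between successive entries to one of K equal strata is 12 × K / 100 months: 0.12 months for a single list, 0.48 for 4 strata and 2.4 for 20. If a physician next sees a patient about 4 weeks later (an assumption), the partner on a single list will usually have been entered already. This stands as a limit on the likely size. It weakens as strata become finer or if lists are kept by hospital, and the article does not say which applies.

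Finally, average guessing improves only from 75% to 71% or 68% with larger fixed blocks. That is true, but the share of certain allocations falls more, from 50% to 33% or 25%. Concealment also does not cure reporting bias in a self-reported outcome; that is a separate problem and is not part of this point.

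**Conclusion.** The point holds as a weakness in a stated design choice. A fixed, published block of 2 with unblinded participants makes up to half of the allocations determined (50 of 100 on one list; 40% to 49% under 40 to 4 assumed equal strata), with guesses right up to 75% of the time, for any recruiting physician who learns the earlier allocation in the same block. Custody of the sequence by a team member, and a concealment sentence that stops short of enrolment, add to the exposure.

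The figures are upper limits that depend on that knowledge. How often recruiters would have it, and how large any resulting bias would be, cannot be calculated from the article. The documents support the statement that concealment is poorly protected, and nothing stronger.

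**What to change.** Replace the fixed blocks of 2 with randomly varying permuted blocks, for example of 4 and 6, and do not disclose the sizes to recruiters. Even if the size were known, fixed blocks of 4 or 6 would bring the determined share to 33.3% or 25%. Undisclosed varying sizes lower it further because block ends are not known; that further gain has not been quantified here.

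Have the outside statistician, or someone with no role in recruitment, hold the list and release each allocation only after consent and baseline assessment. Deleting the custody sentence alone would protect nothing; custody itself has to change. Extend the concealment sentence to enrolment. If recruitment has begun, apply the change to the remaining patients and report it.

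**Cost.** The list is regenerated and one paragraph is amended. Imbalance could reach 2 to 3 patients per stratum, against 1 with blocks of 2, and can add up over strata, so the strata should be few. Eight strata would average 100 / 8 = 12.5 patients each, but 20 would average only 5, too few to fill a block of 6.

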### Intervention

Participants enrolled in the EG will undergo a 4-week prehabilitation programme structured around 3 components: therapeutic exercise, education about back and spine care, and PNE. These interventions will be self-administered by the patients while at home, facilitated by watching a series of educational videos provided by us.

1. Therapeutic exercise

The participants will engage in targeted therapeutic exercises designed to enhance their strength and neuromuscular control of the abdominal and spinal erector muscles. To this end, we will meticulously produce and edit a series of instructional videos to showcase the correct execution of these exercises. These therapeutic exercise videos will span a wide range of difficulty levels to accommodate the varying physical capacities of the individual participants. The baseline scoring obtained from the International Physical Activity Questionnaire-Short Form (IPAQ-SF) will be used to ascertain the most appropriate exercise level for each participant. Thus, videos appropriately tailored to the level of each participant will be distributed within the first week of the prehabilitation programme. During the 4 weeks leading up to the scheduled surgical intervention, participants will undertake 5 weekly sessions of therapeutic exercise at home, guided by the detailed explanations provided in the videos. Furthermore, patients will also undergo mid-programme monitoring by a designated investigator who will establish contact with them to motivate compliance with the exercise regimen and address any queries or concerns the participants may have.

2. Spinal care education

Patients will receive education on spinal care by watching an informative video on the subject. The aim of this material will be to provide information to the patients about the proper execution of movements with their spine and methods for protecting their back. Self-care specifically for the spine will be addressed, including examples of the proper postures to use during the daily activities of life (e.g., walking, standing, sitting, lying down, getting up, sleeping, lifting heavy objects, performing household tasks, and occupational postures, etc.). This material will be distributed within the first week of the prehabilitation programme.

3. Pain neuroscience education

Finally, participants will also be taught the neuroscience of pain by watching educational videos on the topic. The aim of this material will be to help the patients reconceptualise their pain by shifting attention away from the nociception of the affected areas, instead focusing on perceiving pain as an increase in nerve sensitivity and the ascending regulation of the peripheral and central nervous systems. The goal of the PNE will be to reduce patient anxiety and uncertainty and to foster positive expectations and beliefs regarding their scheduled surgeries. The topics covered in the different videos will include education on the physiology of pain, decision-making about undergoing surgery, the goals of surgery, and postoperative recovery [8].

We will produce and edit 3 videos covering the aforementioned monographic content, each lasting approximately 15 minutes. These videos will be distributed sequentially during the last week of the prehabilitation programme, following the recommendations for the optimal timing of PNE in preoperative patients [13, 25]. Patients will be instructed to watch these videos promptly after their distribution and to recall the content provided to them throughout the whole programme. Participants allocated to the CG will be provided with written instructions, by mail, detailing how to perform the back strengthening exercises and will be advised to adhere to the same regimen as the EG during the 4-week prehabilitation programme. In both patient groups, compliance with the exercises will be assessed by daily self-reporting in a logbook. Finally, the anaesthesia and surgical procedures used for the patients in both groups will be similar.

